## Abstract

**Background:**

Affecting approximately 10% of pregnancies, fetal growth restriction (FGR), is the most important cause of perinatal mortality and morbidity. Impaired placental function and consequent mal-perfusion of the placenta is the leading cause of FGR. Although, screening for placental insufficiency based on uterine artery Doppler measurement is well established, there is no treatment option for pregnancies threatened by FGR. The organic nitrate pentaerithrityl tetranitrate (PETN) is widely used for the treatment of cardiovascular disease and has been shown to have protective effects on human endothelial cells. In a randomized placebo controlled pilot-study our group could demonstrate a risk reduction of 39% for the development of FGR, and FGR or death, by administering PETN to patients with impaired uterine artery Doppler at mid gestation. To confirm these results a prospective randomized placebo controlled double-blinded multicentre trial was now initiated.

**Method:**

The trial has been initiated in 14 centres in Germany. Inclusion criteria are abnormal uterine artery Doppler, defined by mean PI > 1.6, at 19^0^ to 22^6^ weeks of gestation in singleton pregnancies. Included patients will be monitored in 4-week intervals. Primary outcome measures are development of FGR (birth weight < 10th percentile), severe FGR (birth weight < 3rd centile) and perinatal death. Placental abruption, birth weight below the 3rd, 5th and 10th centile, development of FGR requiring delivery before 34 weeks` gestation, neonatal intensive care unit admission, and spontaneous preterm delivery < 34 weeks` and 37 weeks` gestation will be assessed as secondary endpoints. Patient enrolment was started in August 2017. Results are expected in 2020.

**Discussion:**

During the past decade therapeutic agents with possible perfusion optimizing potential have been evaluated in clinical trials to treat FGR. Meta-analysis and sub-analysis of trials targeting preeclampsia revealed ASS to have a potential in reducing FGR. Phosphodiesterase-type-5 inhibitors have recently been tested in a worldwide RCT for therapy of established FGR, failing to show an effect on neonatal outcome. The ongoing multicenter trial will, by confirming our previous results, finally provide a therapeutic option in cases at risk for FGR.

**Trial registration:**

DRKS00011374 registered at September 29th, 2017 and NCT03669185, registered September 13th, 2018.

## Background

Affecting approximately 10% of pregnancies, fetal growth restriction (FGR), is the most important cause of perinatal mortality and morbidity. Mortality rates are increased in FGR at any gestational age, and in combination with preterm delivery FGR is associated with higher rates of cerebral palsy, sensory deficits, learning disabilities, and respiratory illnesses [1]. Additionally, individuals born growth restricted are facing lifelong consequences as FGR accounts as developmental origin of adult diseases [2]. The leading cause of FGR is mal-perfusion of the placenta based on insufficient transformation of the uterine arteries and impaired placental function [3]. Uterine artery Doppler measurement is used to determine utero-placental perfusion during pregnancy and thus is established as Screening for placental insufficiency [4, 5].

So far there is no treatment option for pregnancies complicated by FGR and the clinical management is restricted to close monitoring and assessing for the optimal time point of delivery; pondering between intrauterine hypoxia and extrauterine prematurity. Enormous studies have been undertaken to reveal the usefulness of low-dose aspirin (LDA) or antioxidants for secondary and primary prevention of FGR [6, 7]. Although LDA is effective for primary prevention, if initiated before 16 weeks gestation [8, 9], there is still no treatment option for those recognized beyond 20 weeks.

The organic nitrate pentaerithrityl tetranitrate (PETN) is commonly used in the treatment of angina pectoris. As a No-donor it improves perfusion and oxygen supply to the myocardium. In disparity to other NO-donors, aside from vasodilation, PETN also possesses potent endothelium protective qualities by enhancing the expression of antioxidant genes, like heme oxygenase-1 (HO-1), in human endothelial cells [10]. The described biological effects and its well-documented biological safety unveiled PETN to possibly be effective and safe for secondary prevention in pregnancies complicated by and at risk of FGR.

The clinical benefit of the prophylactic use of a NO-donor in pregnant women at risk was first demonstrated by Lees et al. [11]. In this randomized, placebo-controlled, blinded trial glycerol trinitrate patches significantly increase the likelihood of a complication-free pregnancy (*p* = 0.004) and reduced hazard by 73%. Our group could demonstrate a risk reduction of 39% (relative risk RR = 0.609, 95% CI 0.367 to 1.011) for the development of FGR and for FGR combined with perinatal death (RR = 0.615, 95% CI 0.378 to 1.000) through administration of PETN to patients recognized by impaired uterine artery Doppler at mid gestation in a randomized placebo controlled pilot study [12]. Furthermore, a risk reduction of 49% for FGR, as well as for FGR combined with perinatal death (RR = 0.509 (95% CI 0.257 to 1.007), could be achieved in those patients being at high risk, recognized by impaired placental perfusion and an additional history of former pregnancy complications, in the PETN group [12].

These results reveal for the first time, that PETN indeed offers a clinically relevant option to improve fetal outcome. However, the number of 111 enrolled patients does not create enough power to ultimately prove the beneficial effect. Therefore, it is especially important to confirm these results and to verify the efficacy and safety of PETN in a randomized blinded placebo-controlled multicentre-trial with an appropriately calculated sample size. The study protocol of the PETN Trial will be described in detail below.

## Methods/design

### Study objective & design

The aim of this study is to confirm the safety and effectiveness of PETN for secondary prophylaxis of FGR in a prospective, multicenter, randomized, double-blind, placebo controlled, parallel group, interventional trial.

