### Statistical analysis

Baseline characteristics of patients will be compared by descriptive statistics to assess the success of randomization. The primary endpoint (binary variable) will be presented by group-specific incidences. The confirmatory test of the treatment effect stratified for risk-groups will be performed by the Mantel-Haenszel test. Mantel-Haenszel estimates of relative risks and their 95% confidence intervals will be calculated. Primarily, data will be analyzed according to the intent-to-treat (ITT) principle. The ITT-population will include all randomized patients with valid primary outcome data who have received at least one dose of study medication (full analysis data set). The drop-out rate is expected to be 10%. Missing values of the primary endpoint are multiply imputed to confirm the robustness of the main results (sensitivity analysis). All secondary endpoints (binary variables) will be analysed by Mantel-Haenszel methods as described above. In a sensitivity analysis generalized mixed linear models with treatment and risk indicator as fixed, and centre as random factor, will be fitted to adjust for variability between study centres. Explorative analyses of endpoints will be additionally performed for subgroups according to time of delivery and maternal age. AEs/SAEs will be listed. Incidence of events and descriptive statistics (quartiles, mean, standard deviation) of laboratory safety data will be displayed in treatment groups. No adjustment for endpoint multiplicity is planned. All tests will be done at a comparison-wise significance level of 0.05.

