To prove the effects of PETN on adverse pregnancy outcome, particularly the significant decrease in the incidence of FGR and preterm birth, as well as to confirm the the efficacy and safety of PETN, a randomized, double-blinded, placebo-controlled, multi-center trial was initiated.

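### The trial aims to confirm the safety of PETN, but it is sized for efficacy only, and adverse events and death on its own get no between-arm estimate

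*Protocol article*

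**What the plan says.** The Protocol article gives safety equal standing with efficacy. Study objective & design states: "The aim of this study is to confirm the safety and effectiveness of PETN for secondary prophylaxis of FGR". The Discussion closes on the same purpose: "as well as to confirm the the efficacy and safety of PETN". The Background speaks of a trial "to verify the efficacy and safety of PETN in a randomized blinded placebo-controlled multicentre-trial with an appropriately calculated sample size".

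Proposed sample size/power calculations derives 290 evaluable and 324 randomised women from one outcome, FGR or perinatal death. It mentions no safety outcome, rate or margin.

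The safety analysis is set out in Statistical analysis: "AEs/SAEs will be listed. Incidence of events and descriptive statistics (quartiles, mean, standard deviation) of laboratory safety data will be displayed in treatment groups". The same section plans a Mantel-Haenszel test and relative risks with 95% confidence intervals for the primary endpoint, and the same methods for all secondary endpoints. By the Abstract and Primary outcome measures, the secondary endpoints include placental abruption, NICU admission, ventilation, intraventricular haemorrhage and necrotising enterocolitis. Primary outcome measures places death in two composites: with FGR (primary), and with severe FGR and abruption (secondary).

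**The concern.** Confirming safety means showing that harm above some size is unlikely. That takes an estimate of the PETN-placebo difference and an upper limit on it. For adverse events the plan provides neither, so it supports a description of what was seen and not a confirmation.

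Two gaps matter most. First, overall and maternal SAEs and discontinuation for side effects get no comparison. Compliance/rate of loss to follow up reports that two pilot patients on PETN stopped because of possible side effects (dizziness and headache), so tolerability was a known question. Second, death is not analysed on its own. A composite expected to fall because FGR falls can hide a rise in a much rarer component.

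PETN is given here as prophylaxis in pregnancy. Readers will want to know how large an excess of harm is still compatible with the data, and the stated displays do not show it.

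**Working it through.** **1. The plan's own figure.** Inputs from the sample size section: placebo rates 0.42 (low risk) and 0.69 (high risk), low:high ratio 2:1, odds ratio 0.5, two-sided 0.05, 80% power. Allocation of 1:1 is assumed because the article does not state it.

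- PETN rates: odds 0.5 × 0.42/0.58 = 0.362 give 0.266; odds 0.5 × 0.69/0.31 = 1.113 give 0.527.
- With stratum weights w = 2/3 and 1/3, placebo rate p, PETN rate q and m = (p + q)/2: D = Σw(p − q)/4 = 0.0393; V0 = Σw·m(1 − m)/4 = 0.0574; V1 = Σw[p(1 − p) + q(1 − q)]/8 = 0.0559.
- N = [(1.96√V0 + 0.842√V1)/D]² = 289.3, so 290, as stated.
- Dropout: 290/0.9 = 322.2, so 323, or 324 for two equal arms.

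The efficacy sample size is sound. No safety quantity enters it.

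**2. What this size offers for a safety event.** The placebo rates below are assumptions. Power is for a two-sided 0.05 two-proportion test of a doubling, by summing exact binomial probabilities over all outcome pairs.

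| Placebo → PETN | 162 per arm | 145 per arm |
|---|---|---|
| 1% → 2% | 10% | 9% |
| 2% → 4% | 17% | 15% |
| 3% → 6% | 25% | 23% |
| 5% → 10% | 40% | 36% |
| 7% → 14% | 55% | 50% |
| 10% → 20% | 72% | 68% |
| 12% → 24% | 81% | 77% |

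By the normal approximation, power passes 50% at a placebo rate of about 6.4% with 162 per arm and 7.1% with 145 per arm.

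**3. What an apparently reassuring result leaves open.**

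- 5/162 in each arm (3.1%): Wilson limits are 1.33% and 7.02%. The Newcombe upper limit for the difference is √[(7.02 − 3.09)² + (3.09 − 1.33)²] = 4.3 points, more than the 3.1% rate itself.
- 0/162 on PETN: the upper 97.5% limit is 1 − 0.025^(1/162) = 2.3%.

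**4. Death inside the primary composite.** Expected placebo rate: 2/3 × 0.42 + 1/3 × 0.69 = 0.51. Expected PETN rate: 2/3 × 0.266 + 1/3 × 0.527 = 0.353. The planned effect is therefore a fall of about 16 points. A death in a pregnancy already counted as FGR does not change the composite at all. Each 1-point excess of deaths without FGR offsets only 1 of those 16 points. The interval for the composite thus says little about mortality.

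**The case against.** **The gravest fetal and neonatal harms are already compared with intervals.** This stands for abruption, NICU admission, ventilation, intraventricular haemorrhage and necrotising enterocolitis. A reader might infer that the whole safety plan is listings and incidences, and the article does not support that. It does not stand for death. The Abstract names perinatal death among the primary measures, but Primary outcome measures defines the endpoint as a composite with FGR, and no separate analysis of death is stated.

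**A doubling need not be missed.** This stands. A reader might infer that a trial of this size would usually miss a doubling of serious events in general. That depends on a base rate the article does not give. In a population with placebo rates of 0.42 and 0.69 for the primary composite, overall SAE incidence could well lie above 6 to 7%, and a doubling would then usually be detected.

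**No rule says that no difference means safe.** This stands. A reader might infer such a rule from the word confirm, but none is stated. Nor does the Background claim a sample size for safety: its remark answers the pilot's lack of power for benefit.

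**Safety tables belong in the full protocol or SAP.** This is partly right. Details may well sit there, and their absence would be no fault. But the article does not leave the safety analysis open: it states a descriptive one next to a confirmatory aim, and those two statements conflict.

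**A monitoring board and four-weekly safety checks exist, and arm-specific incidences will be shown.** This is true. But monitoring during the trial is not a final safety analysis, and a crude interval derived by the reader would not be stratified by risk.

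**Conclusion.** The point holds as a mismatch between a stated aim and a stated analysis. The trial sets out to confirm safety, is sized on efficacy alone, and plans only description for overall and maternal adverse events and discontinuation, with death confined to composites with FGR.

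The size depends on event frequency. With 162 per arm, a doubling would be missed more often than not below a placebo rate of about 6 to 7% and usually found above it. With five events in each arm, an excess of up to 4.3 points is not excluded. These figures rest on 1:1 allocation, assumed placebo rates and a test that the plan does not schedule, so they show what the sample can tell us and do not predict the result. The primary efficacy analysis and its sample size are unaffected. The change is worth making because it is cheap and the safety claim is prominent.

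**What to change.** 1. In Study objective & design and at the end of the Discussion, restate the safety aim as estimating or describing the safety of PETN, and say that the sample size is set for efficacy.
2. In Statistical analysis, add risk-stratified Mantel-Haenszel estimates of PETN versus placebo (risk difference or relative risk) with 95% confidence intervals, in all women who took study drug, for: any SAE; fetal or neonatal death on its own; discontinuation for side effects; and headache/dizziness.
3. Report the upper limit of each interval as the largest excess not excluded.

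The article already plans to record adverse events, maternal symptoms and perinatal outcome, and Mantel-Haenszel estimation is already used for the endpoints. The cost is a few more table columns and a more modest safety claim. No extra patients are needed.

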### Ethics statement

Ethical approval has been obtained from the ethical committee of the University Hospital of Jena as leading committee (Institutinal review board (IRB) Friedrich Schiller University, Jena) (5085–02/17). Each of the 14 German study centers obtained ethical approval of their local committees (IRB Universitäts-Kinderklinik, Kiel, IRB Hannover Medical School, Hannover, IRB Medical School, Rheinischen Friedrich-Wilhelms-University, Bonn, IRB State Office for Health and Social Affairs (LAGeSo) Berlin (two centres), IRB of the state of Saxony-Anhalt, Halle (two centres), IRB Medical School, Leipzig, IRB Technical University Dresden, IRB Medical School, Eberhard-Karls-University, Tübingen, IRB University of Ulm, IRB Ludwig Maximilian University, Munich, IRB national Medical association Bavaria, Munich), which than were referred to the Jena committee before approval was issued. Written informed consent must be obtained before the performance of any protocol related procedures that are not part of usual subject care.

### Inclusion criteria

Eligible patients for the proposed trial are pregnant women recognized to be at risk of adverse pregnancy outcome associated with FGR at mid gestation. Since poor placental function and mal-perfusion of the placenta is recognized to cause FGR [3] impaired placental flow measurement is strongly associated with the development of FGR. A mean pulsatility index >95th percentile according to Cnossen et al. predicts FGR with a sensitivity of 18% with a specificity of 95% in a general population and a sensitivity of 58% for any FGR in a high risk population with a specificity of 75% [4]. The risk to develop FGR is in general higher in women with a medical history of chronic hypertension, diabetes mellitus type 2, systemic lupus erythematodes or antiphopholipid antibody syndrome and in those with prior history of adverse pregnancy outcome associated with FGR (late pregnancy loss, stillbirth, abruption placentae, preterm delivery, preeclampsia or HELLP-syndrome) [13]. Accordingly, at least one third of the pregnant women diagnosed with impaired perfusion of the uterine arteries at mid gestation will develop FGR and associated adverse pregnancy outcomes. In the presence of additional risk factors this likelihood will rise considerably.

Consequently, the Inclusion criteria are impaired uterine artery Doppler ultrasound, defined by a mean Pulsatility Index (PI) greater than 1.6 (> 95th centile of German reference population, PIA Fetal Database, Version 4.00 and higher, Viewpoint, Germany; [14]), singleton pregnancy at 19^0^ to 22^6^ weeks of gestation who are over 18 years old and provide informed consent.

### Exclusion criteria

To ensure the inclusion of solely placental reasons for FGR and for ethical reasons, exclusion criteria are multiple pregnancies, fetal chromosomal or suspected major structural defects, circumstances predicting adverse pregnancy outcome other than due to FGR, like premature rupture of membrane or cervical insufficiency at the time of enrolment, participation in any other clinical trial and maternal disease defined as contraindication for intake of PETN.

### Primary outcome measures

As primary efficacy endpoint development of FGR (< birth weight below the 10th centile) or perinatal death as a composite outcome was proposed in accordance to the pilot study [12]. Key secondary endpoints are severe morbidity and mortality as composite of severe FGR, intrauterine or neonatal death or placental abruption, birth weight below the 3rd, 5th and 10th centile according to Voigt [15], development of FGR requiring delivery before 30 and before 34 weeks` gestation, spontaneous preterm delivery before 34 weeks and before 37 weeks gestation, rate of neonatal intensive care unit admission and neonatal complications like the need of ventilation, occurrence of intraventricular hemorrhage II – IV ° or necrotized enterocolitis.

### Determination of primary and secondary measures

The gestational age was calculated from a certain last menstrual period date and confirmed by first trimester measurement of the crown-rump-length. Weight percentiles are derived from gestational age and weight according to the German standards by Voigt [15]. Falling below the 10th weight percentile in combination with impaired uterine perfusion (inclusion criteria mean PI of > 1.6) is defined as FGR [16].

Development of severe FGR is defined as birth weight below the 5th centile. Preterm delivery is determined from gestational age at birth.

### Methods against bias

Patients will be randomly assigned to treatment groups in blocks of varying size. Randomization will be stratified by center and by an indicator for low or high risk of FGR. Patients will be classified as high risk in case of pre-existing hypertension, pre-existing diabetes or obstetric history of FGR, late pregnancy loss, stillbirth, abruption placentae, preterm delivery, preeclampsia or HELLP-syndrome. All others are at low risk. PETN and placebo will be administered in a double-blind fashion. Primary analysis will be performed in the intent-to-treat population.

### Proposed sample size/power calculations

Sample size calculation is based on results generated from our pilot trial [12]. Since additional risk factors increase the risk of FGR a stratified randomisation and analysis is planned for two strata. A 2:1 ratio was observed for low and high risk patients in the trial. Proportion of FGR or perinatal death was 0.42 in the low-risk and 0.69 in the high-risk stratum of the placebo group. We discovered an odds ratio of 0.41 (PETN vs. placebo) in the pilot trial. More conservatively, we want to be able to find a 50% risk reduction (i.e. an odds ratio of 0.5) in the here proposed study, which would still be of profound clinical relevance. Accordingly, we will need a sample size of 290 patients to detect this treatment effect by a Mantel-Haenszel test with a power of 80% at a two-sided alpha-level of 0.05 (nQuery 7.0). Assuming a dropout rate of about 10% a total of 324 patients should be randomized.

### Compliance/rate of loss to follow up

During the pilot study the reported compliance was markedly high. Of the 111 patients included in the study only 5 discontinued intervention (5%), of whom 2 in the verum group stopped intervention due to potential side effects (dizziness and headache). This high compliance was likely to be related to the high burden derived from the worry about the unborn.

The number of patients calculated for allocation to the PETN trial accounts for a more conservative dropout rate of 10%, due to the particularly good compliance of pregnant women, especially those to be at risk for neonatal complications. For the primary outcome, robustness of the results regarding missing values will also be analyzed.

### Recruitment

Patients eligible are recruited from those pregnant women presenting during prenatal care for routine or risk guided midtrimester ultrasound screening for fetal structural anomalies including the assessment of utero-placental perfusion. 5% are expected to demonstrate impaired utero-placental flow with a mean PI exceeding the 95th centile indicating a risk for IUGR. In our pilot trial an estimate of 50% of the eligible patients were enrolled per year. Accordingly, to recruit 324 patients within 18 months we need to identify 650 women with impaired utero-placental perfusion at mid gestation. Based on the fact, that of all women presenting for mid gestation ultrasound 5% will meet the inclusion criteria (mean PI >95th centile (> 1.6)) a cohort of about 13,000 women will be needed to recruit from. To enlarge the cohort, study centers are asked to cooperate with affiliated outpatient facilities, run by gynecologist holding a DEGUM II or III qualification. Patients recruited in the affiliated facilities will then be sent to the participating study center for verification of eligibility and study inclusion. (Fig. 1).

